***2. Statistical Analysis***

**Primary Outcomes**

We will randomize 13 participants to each of the three study arms (control, 150 min∙wk^-1^, 300 min∙wk^-1^), to achieve 10 per group who complete the study (76% completion rate). Participants who have a cancer recurrence during the study will be excluded from the primary outcome analysis. The sample size is powered for the primary outcome biomarkers (sICAM-1 and sVICAM-1) with a hypothesis for a linear trend. The standard deviation of sICAM-1 and sVCAM-1 are 30 and 103 units, respectively. Against the hypothesis of a dose-response relationship with decreases of 22 and 44 units for low- and high-dose respectively for sICAM-1 and 74 and 148 units for sVCAM-1, 30 subjects provide 80% power for two, two-sided 0.025 tests (one for sICAM-1 and one for sVCAM-1, with the Type I error adjusted to maintain the experiment-wise error rate of 0.05). These reductions are consistent with prior exercise interventions in non-cancer survivorship populations, where clinically significant reductions in sICAM-1 and sVCAM-1 occur with 30 and 75 unit changes, respectively.[99-103]

The feasibility of exercise will be quantified by comparing the proportion of participants in each group who achieve ≥80% of their prescribed exercise dose. The incidence of exercise dose-alteration will be quantified by comparing the proportion of participants who require a dose-reduction or cessation of exercise in each group. The indication for the dose-reduction or cessation will also be described qualitatively. As this aim intends to describe feasibility, we state no directional hypothesis. For the primary biomarker outcomes, we will use a linear mixed-effects regression to compare the change in biomarker levels for each group while controlling for other variables likely to influence sICAM-1 and sVCAM-1 (in addition to the effects from treatment group). Potential confounders (e.g., change in diet, sleep, or body weight) will be screened using univariate models; those that appear to be associated with the outcome will be entered sequentially in multivariate models. We will initially fit models including dose as a linear term, and assess model fit using standard methods. Alternatives to a linear dose trend include transformations of dose such as average actual dose, log-transformed dose per week, or second-order polynomial (i.e., dose and dose^2^). In the event that a dose-response relationship does not exist, we will compare each of the two intervention groups (low- and high-dose exercise) to the control arm separately. Using a two-sided t-test we will have 80% power to detect a difference in of 32 units for sICAM-1 and 112 units for sVCAM-1, utilizing the sequential testing procedure of Benjamini and Hochberg to protect the family-wise error rate.[155]

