**BACKGROUND**

**Colon Cancer Treatment and Prognosis.** There are 103,000 people diagnosed annually with colon cancer (CC) in the United States.[1] Among those diagnosed, 39% will have localized CC (confined to the primary site), 36% will have regional CC (spread to regional lymph nodes), and 20% will have metastatic disease (spread to distant organs).[1] Among those without metastatic disease, 5-year survival rates for localized and regional CC are 90% and 70%, respectively.[1] Surgery is the primary treatment modality for local and regional CC, with curative resection occurring in 80-85% of patients.[2] Those with regional disease may also receive adjuvant chemotherapy.[3,4] Despite the efficacy of resection and adjuvant chemotherapy, 30-50% of patients with local and regional CC develop recurrent cancer.[2,5] Eighty percent of recurrences occur in the first three years after treatment, and 91% of patients who develop a recurrence by three years, die before five years.[6] The high rate of recurrent disease is a critical barrier to promote the health and longevity of CC survivors. An approach to reduce this barrier is to develop interventions to minimize recurrence that CC survivors can accomplish autonomously, such as lifestyle and behavioral modification.

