**Colon Cancer Recurrence.** Cancer recurrence and metastasis are the leading causes of morbidity and mortality in CC, marking the transition from localized, potentially curable to disseminated, usually incurable disease.[7,8] CC recurrence is typically characterized by locoregional relapse and/or distant metastasis to the liver or lung.[5] A key condition for CC recurrence is that existing micro-metastases or circulating tumor cells (CTCs) be present in the body at the time of curative treatment.[8,9] Existing micro-metastases have been difficult to characterize given their absence with radiographic imaging and with other forms of staging. Autopsy studies suggest 66% of metastases in CC are explained by vascular blood flow alone.[9] Given the challenge to identify micro-metastases, characterizing biomarkers that promote existing tumor growth and dissemination of CTCs in the vasculature may advance knowledge of CC recurrence and progression. For example, 25-55% of non-metastatic CC survivors have measureable volumes of CTCs in their blood after completing curative treatment.[10] The presence of CTCs predicts recurrence, tumor progression, and survival among CC survivors.[11-16] Among 438 patients with local or regional CC (stages I-III), 31% had tumor cells in peripheral blood after completing treatment, and the presence of CTCs was associated with a 29-fold increase in recurrence (p<0.001).[12] The implementation of CTC technology into clinical care has been subject to debate.[17] Little evidence currently exists to leverage knowledge about CTCs to improve clinical outcomes.[17] However, many of these previously published reports documenting relatively low concentration of CTCs in patients with early colon cancer and in those with frank metastases utilized the CellSearch^®^ system to quantify CTCs, the first FDA-approved device to identify CTCs.[18,19] We have developed an alternative detection technology, GEDI (geometrically enhanced differential immunocapture), which has been shown to be superior to CellSearch^®^ in head-to-head studies.[20] In CC, we have been able to detect up to 100-fold greater CTCs compared to CellSearch^®^ (unpublished data), and approximately 80% of patients with advanced CC contained CTCs. Thus, our innovative approach provides unsurpassed sensitivity in quantifying CTCs. Underscoring this sensitivity, we have detected circulating epithelial cells (CECs) in the bloodstream of patients at high-risk for tumor formation, yet do not have a diagnosis of cancer. In mouse models of spontaneous cancer, contrary to current models, CECs and CTCs can seed the bloodstream prior to the formation of clinically (radiographic) detectable tumors.[21] Seeding of the blood circulation by CECs also occurs in patients in the absence of clinically (radiographic) detectable tumors. We and others have shown that CECs can be detected in the bloodstream of patients with advanced precancerous adenomas of the colon[22] (and unpublished). This is of interest since these are patients with no diagnosis of cancer, but may harbor occult neoplastic disease. Based on our results, it is likely that elaboration of CTCs occurs early in the recurrent metastatic cascade. The sources of CTCs are likely distant micro-metastatic foci. We hypothesize that cancer cells disseminate via the circulation during the earliest stages of recurrent metastatic growth, mirroring what occurs during the primary tumor setting. If this does indeed occur, we are uniquely situated to detect this phenomenon using the GEDI device. By implementing the GEDI technology in our study, we will have preliminary data to suggest if exercise is one such intervention to improve outcomes by acting through cell-adhesion and other pathways implicated at the intersection of CC recurrence and exercise.[23-26] If our hypothesis is correct that exercise will serve to delay or inhibit the progression of recurrent or metastatic CC, this may be reflected in CTC concentration. In conclusion, identifying and intervening on pathways that act to promote the growth of existing micro-metastases and stimulate CTC activity may be one means to reduce recurrent disease among CC survivors.[7-9]

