sICAM-1 is not expressed in healthy colonic cells, and over expressed in CC tumor cells.[31,38] sICAM-1 expression increases in dose-response fashion with tumor growth and progression,[27] and predicts survival, lymph node and distant metastases, and is associated with serum carcinoembryonic antigen (CEA), the clinical biomarker used to monitor CC recurrence and tumor progression.[39] Among stage II CC survivors, elevated sICAM-1 levels were associated with an 8.8-fold increase in risk of mortality (p=0.001).[39] The relationship between sICAM-1 and CC is well-established as other investigative groups have reached similar conclusions about the predictive significance of sICAM-1 and CC.[27,32,40] Similar to sICAM-1, sVCAM-1 is expressed in dose-response fashion and predicts tumor growth and progression.[27,41] sVCAM-1 is chronically elevated for at least one-month after surgical resection for CC, which may promote growth of micro-metastases and aberrant CTC behavior immediately after surgery.[42] An animal model confirmed the intraperitoneal microenvironment after surgery enhances the activity of disseminated CTCs as hypothesized.[43] sVCAM-1 additionally predicts survival,[27] recurrence,[44] lymph node and distant metastases.[27,45] Among 100 stage I-IV CC survivors, elevated sVCAM-1 levels were associated with an 11.1-fold increase in liver metastasis (p=0.028).[45] The importance of sVCAM-1 and CC as described above has been observed by others.[27,32,40-42,44,46]

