Prior literature supports the hypothesis that sICAM-1 and sVCAM-1 are active molecules of the cancer recurrence cascade, specifically associated with growth and progression of existing micro-metastases in melanoma,[47] CC,[27] and in in vivo studies.[48] sICAM-1 and sVCAM-1 play important roles in promoting CTC extravasation to distant tissues and recruitment of pro-tumorigenic leukocytes to existing micro-metastases. sICAM-1 and sVCAM-1 cleavage and release into the circulation occurs during upregulation and engagement of inflammatory and proangiogenic factors in cells with receptors specific to these molecules, i.e., at the earliest stages of dissemination at the distant organ sites.[49] We hypothesize that exercise may inhibit both seeding of distant organs by CTCs and the cultivation of the angiogenic milieu that is thought to be required for metastatic tumor growth. As a first step towards addressing this hypothesis, we will measure serum sICAM-1 and sVCAM-1 given their importance in mediating these processes.

**Colon Cancer and Visceral Adipose Tissue.** The two main compartments in which adipose tissue is stored include: 1) subcutaneous adipose tissue (SAT) and 2) VAT.[50,51] SAT represents a usual physiologic buffer to store excess energy.[51] When the storage capacity of SAT is exceeded, VAT is accrued. Accordingly, 80–90% of all body fat is SAT, and the remaining 10–20% is VAT.[52] The cells that constitute adipose tissue are known as adipocytes. The adipocytes that constitute VAT are physiologically and pathologically distinct from SAT.[51,52] The adipocytes of VAT are more deleterious to health than the adipocytes of SAT, due to their metabolic secretion of bioactive compounds such as adipokines, cytokines, hormone-like factors, and other metabolites.[53,54] The deleterious metabolic activity of VAT, coupled with anatomic proximity to vital organs, and direct drainage into portal venous vasculature (a location of many CC recurrences), manifests as a pro-tumorigenic milieu.[55]

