
**Colon Cancer and Physical Activity**. Increasing levels of post-diagnosis physical activity (PA) are associated with a 42% improvement in disease-free survival,[24] 40% reduction in cancer recurrence,[24] and 45-71% reduction in CC-specific mortality.[24-26] The evidence also suggests PA improves outcomes in dose-response fashion, such that CC survivors who engage in larger volumes of PA have more favorable disease free survival (p_trend_=0.01), recurrence (p_trend_=0.03), and CC-specific mortality (p_trend_=0.008).[24-26] The relationship between PA volume and CC outcomes has been depicted as a linear or quadratic pattern using smoothed splines.[24,26] The splines suggest 225 min∙wk^-1^ may be the minimum threshold necessary to improve CC outcomes, as is prescribed in current ongoing studies.[81,82] However CC outcomes continue to improve beyond 225 min∙wk^-1^, suggesting that larger doses may be more efficacious.[24,26] PA volume >400 min∙wk^-1^ does not appear to confer additional improvements in these outcomes. Categorically, a dose of ~300 min∙wk^-1^ of moderate-intensity PA appears necessary to reduce recurrence, improve disease-free survival, and improve CC-specific mortality.[24-26] It remains unknown if larger doses of exercise are behaviorally feasible and have tolerable safety and symptom profiles.[24] Interestingly, levels of PA before diagnosis of CC do not associate with CC-specific mortality.[25,61,83] This suggests the hypothesized pathways in which PA associate with primary prevention of CC may differ from that of secondary prevention of CC.[84] The American College of Sports Medicine (ACSM) and the American Cancer Society published guidelines for cancer survivors, recommending 150 min∙wk^-1^ of moderate intensity PA.[85,86] This recommendation is inconsistent with the dose of PA necessary to reduce recurrence, and improve CC-specific mortality indicated by the epidemiologic literature. Several reviews, including The ACSM statement for exercise among cancer survivors, have called for more research to empirically investigate the dose-response effects of exercise,[86-89] and the safety profile of prescribing larger doses of exercise.[86,90] Among 295 breast cancer survivors who participated in our PAL trial,[91,92] a yearlong weight-lifting study, 21% required a dose-modification or cessation of weight-lifting as a result of a health event.[93] These findings parallel evidence from adults aged ≥70 years in an exercise trial, where 34% of participants had a healthcare event that influenced their completion of the initial prescribed dose of exercise.[94] The insufficient evidence regarding the specific dose of exercise necessary to improve CC outcomes likely serves as a barrier to the dissemination of exercise to CC survivors. Clinicians have noted they do not know what tell their patients about exercise.[95] The majority of clinicians (57%) provide no recommendation about PA.[96,97] Obtaining systematic data pertaining to dose-reduction or cessation of exercise is critical to future optimization of the allocation of behaviorally intensive resources, such as cancer rehabilitation and exercise programming. These data may be fruitful as exercise moves towards the forefront for consideration as a standard of care for cancer survivors, similar to cardiac rehabilitation.[96]

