***6. Risk/Benefit Assessment***

Once participants are randomized, a certified clinical exercise physiologist will review their current exercise habits and baseline fitness levels and develop a plan to gradually increase the minutes of exercise each week to the prescribed dose. The intensity of their aerobic exercise will be objectively monitored and recorded using heart rate monitors. The certified clinical exercise physiologist will review the objective recording produced by the heart rate monitor each week, and ask the participant if they are experiencing any symptoms that would preclude an increase or maintenance of the currently prescribed dose of exercise. The participants medical care team will be informed of symptom changes and consulted regarding whether is it appropriate to dose-reduce the exercise or cease exercise training all together. In our prior exercise study, the [name] research laboratory suggests 20% of participants will require exercise dose modifications during the 6 month intervention. Participants who are found to have recurrent cancer will be allowed to continue participation in the study, unless their medical oncologist or other physician asks them to stop or reduce their level of exercise. Participants who are found to have a recurrence will be excluded in data analysis. Study staff will work closely with the medical team to ensure the participant receives appropriate medical and psychosocial care and follow-up as necessary.

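### Participants whose cancer recurs after randomisation are dropped from the analysis, although the protocol links recurrence to both exercise and the primary biomarkers

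*Protocol*

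**What the plan says.** Under Statistical Analysis, Primary Outcomes, the protocol states: "Participants who have a cancer recurrence during the study will be excluded from the primary outcome analysis". Section 6, Risk/Benefit Assessment, gives a wider rule: "Participants who are found to have a recurrence will be excluded in data analysis". The same paragraph says "Participants who are found to have recurrent cancer will be allowed to continue participation in the study", unless a physician asks them to stop or reduce exercise. No reason is given for the exclusion, and no analysis that keeps these participants is described.

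The Background ties recurrence to the intervention and to the primary endpoint:

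- **Exercise and recurrence.** The section on recurrence reasons from the premise "If our hypothesis is correct that exercise will serve to delay or inhibit the progression of recurrent or metastatic CC". The section on physical activity cites a "40% reduction in cancer recurrence" with higher post-diagnosis activity.
- **Recurrence and biomarkers.** "Prior literature supports the hypothesis that sICAM-1 and sVCAM-1 are active molecules of the cancer recurrence cascade", and "sICAM-1 expression increases in dose-response fashion with tumor growth and progression".

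**The concern.** Randomisation makes the three arms comparable at baseline. Removing participants for something that happens later keeps them comparable only if that event, and its relation to the outcome, are the same in every arm. Here the protocol expects the opposite. If exercise prevents some recurrences and recurrence raises the biomarkers, the exclusion takes high values mainly out of the control arm and shrinks the apparent benefit.

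The direction is not guaranteed. Exercise participants have supervised sessions with a symptom review, while controls have weekly telephone calls, so recurrence could be noticed at different rates even if exercise does nothing.

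Two things are at stake. The first is the biomarker effect estimate, which the Overall Objectives say will inform a phase III trial. The second is the descriptive results. A physician's request to stop or reduce exercise after a recurrence is a dose alteration, and dose alteration is part of the primary aim. Read literally, the Risk/Benefit rule removes that participant, and so the event, from the count.

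**Working it through.** **Inputs from the protocol**

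- Primary Outcomes analysis: 13 randomised and 10 completers per arm; SD 30 (sICAM-1) and 103 (sVCAM-1); decreases of 22 and 44, and of 74 and 148; two-sided alpha 0.025 per biomarker; 80% power with 30 participants.
- Background: 30-50% recur; "Eighty percent of recurrences occur in the first three years after treatment"; five-year survival 90% (localised) and 70% (regional); 91% of those recurring by three years die before five; 40% lower recurrence with activity.

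**Assumptions not in the protocol**

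- The SD is that of the change.
- Recurrences are spread evenly over the first three years.
- A recurrent participant's change lies g SD above that of the others, with g from 1 to 3.
- The cited 40% reduction applies to high dose against control within six months.

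**1. The plan's power.** With equal arms, the linear trend compares high dose with control, and the low-dose mean has zero weight.

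- Noncentrality = difference / (SD × √(2/n)).
- sICAM-1: 44 / (30 × √0.2) = 3.28. sVCAM-1: 148 / (103 × √0.2) = 3.21.
- With 28 degrees of freedom, power is 81.3% and 79.6%. The stated 80% reproduces.

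**2. Expected exclusions over six months**

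| Basis | Six-month risk | Of 39 |
|---|---|---|
| Even spread: 0.30 × 0.80 / 6 to 0.50 × 0.80 / 6 | 4.0-6.7% | 1.6-2.6 |
| Constant hazard: 1 − (1 − 0.24)^(1/6) to 1 − (1 − 0.40)^(1/6) | 4.5-8.2% | 1.7-3.2 |
| Ceiling implied by survival: (0.10/0.91)/6 to (0.30/0.91)/6 | 1.8-5.5% | 0.7-2.1 |

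About 1 to 3 participants is a fair summary. The chance of at least one exclusion, 1 − (1 − risk)^39, is 80-96% on the first two rows and 51-89% on the third.

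**3. Expected bias.** The exclusion shrinks the high-dose versus control contrast by g × SD × (control risk − high-dose risk).

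- Control risk 4%, high dose 0.6 × 4% = 2.4%: 30 × 0.016 × g = 0.5 to 1.4 units.
- Control risk 7%, high dose 0.6 × 7% = 4.2%: 30 × 0.028 × g = 0.8 to 2.5 units.
- Overall this is 0.5-2.5 units, about 1-6% of 44. It is zero if recurrence risk and displacement are equal across arms.

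**4. One actual exclusion among 10.** The arm mean moves by g × SD / 10.

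- sICAM-1: 3 to 9 units, or 7-20% of 44.
- sVCAM-1: 10.3 to 30.9 units, or 7-21% of 148.
- In the control arm this lowers the apparent benefit; in the high-dose arm it raises it. In the low-dose arm it leaves the trend estimate essentially unchanged.

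**5. Power, if exclusions come on top of planned attrition**

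| Analysed | sICAM-1 | sVCAM-1 |
|---|---|---|
| 30 | 81% | 80% |
| 28 | 78% | 76% |
| 27 | 76% | 74% |

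**The case against.** The best defence is that the trial asks about biological efficacy in survivors without metastatic disease or planned chemotherapy. A sample taken after re-treatment may reflect that treatment; the Background itself says sVCAM-1 stays raised for at least a month after resection. A disease-free target is therefore arguable. That supports reporting such an analysis. It does not support making it the only one, because who remains disease-free may depend on the arm.

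Size is the second defence, and much of it stands. Six months is short, high dose reaches its full volume only in week 10, and the 40% figure is an observational association. The 1-3 SD displacement has no source in the protocol.

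Four stronger readings are tempting but unsupported:

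- *The shift is 27-41% of the effect.* That sets 6-9 units against the 22-unit low-dose effect. The powered test is the trend, whose contrast is 44 units.
- *Power falls to 78%.* The exclusion is stated directly after the allowance of 13 randomised for 10 completers, and Limits of Assumptions expects 80% completion (0.80 × 39 = 31.2). One or two exclusions may already be absorbed.
- *Safety reporting loses these participants.* Data and Safety Monitoring requires reporting of events of grade 3 or higher and collects injuries and major medical events on all participants. Neither is clearly affected.
- *The narrower rule protects adherence and dose alteration.* Both are analysed under the Primary Outcomes heading, although the outcome list calls them secondary, so even that rule may cover them. The clearest gap between the two rules is visceral fat and insulin.

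**Conclusion.** The point holds as a flaw in the analysis population, not as an arithmetic error; the stated power reproduces. The protocol excludes on a post-randomisation event that its own rationale links to treatment and outcome, and it states the scope of the exclusion in two different ways. About 1 to 3 of 39 participants would be affected. The average bias is modest and rests on an assumed displacement and an assumed difference between arms. A single exclusion in the control or high-dose arm would nevertheless be visible with 10 per arm.

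A reader might infer that the comparison is invalid or certainly biased against exercise. The documents support neither: systematic bias needs recurrence, or its biomarker effect, to differ between arms, and the direction could go either way. In a feasibility study of this size the change should be made, but the flaw does not undermine the trial.

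**What to change.** In Statistical Analysis, Primary Outcomes, replace the exclusion with text such as: *All randomised participants are analysed in their assigned arm regardless of cancer recurrence, using all available baseline and six-month measurements in the linear mixed model. An analysis excluding participants with recurrence is reported as a sensitivity analysis.* State that the six-month sample is collected from recurrent participants who continue.

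Limiting the analysis to participants who have a six-month sample would not be enough. That again selects on something that happens after randomisation, and recurrent participants may be the likeliest to lack the sample.

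Align section 6, Risk/Benefit Assessment, with this wording, so that recurrent participants stay in the adherence, dose-alteration, visceral fat and insulin summaries.

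The cost is wording and one extra model run. Samples taken after new cancer therapy may add variance to the primary analysis; the sensitivity analysis shows how much this matters.
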